# Online Self-Management Support for Family Caregivers to Help Them Manage Behavior Changes in Their Relative With Dementia: Study Protocol for a Randomized Controlled Trial and a Process Evaluation

**DOI:** 10.2196/resprot.8365

**Published:** 2017-11-28

**Keywords:** dementia, family caregivers, self-management, behavior problems, Internet, eHealth, RCT, process evaluation

## Abstract

**Background:**

Online interventions are potentially effective ways to support family caregivers in the management of behavior changes in their relative with dementia.

**Objective:**

The objective of this paper is to present the design of a study evaluating and comparing 3 intervention arms for online self-management support.

**Methods:**

A randomized controlled trial (RCT) will be conducted with a total of 81 family caregivers of community-dwelling people with dementia in the Netherlands. Family caregivers will be randomly allocated to one of the following intervention arms: (1) a major self-management support intervention consisting of personal email contacts with a nurse specialized in dementia care, online videos, and electronic bulletins (e-bulletins); (2) a medium self-management support intervention consisting of only online videos and e-bulletins; and (3) a minor self-management support intervention with only e-bulletins. The primary outcome is the self-efficacy of the family caregiver. The secondary outcomes are the behavior problems of the person with dementia as reported by the family caregiver, and positive and negative aspects of the relationship. Background characteristics (eg, type of family relationship) will also be assessed. All data for the RCT will be collected via online questionnaires, administered before the intervention (T0), after 6 weeks (T1), and after 12 weeks (T2). Alongside the RCT, a process evaluation will be conducted, based on a number of evaluation questions and semi-open interviews with family caregivers.

**Results:**

Data collection will be completed in August 2017. Study results will be reported in early 2018.

**Conclusions:**

The study will shed more light on the effect of online self-management support interventions and insights will be gained into whether a major intervention, consisting of personal email contacts with specialized nurses, videos, and e-bulletins, has more effect than smaller online interventions. This is relevant in an age with increasing numbers of people with dementia, growing pressure on family caregivers, more and more people using the Internet, and increasing healthcare costs.

**Trial Registration:**

Nederlands Trial Registry (NTR): NTR6237; http://www.trialregister.nl/trialreg/admin/rctview.asp?TC=6237 (Archived by WebCite at http://www.webcitation.org/6v0S4fxTC)

## Introduction

### Background

Dementia is a progressive disorder characterized by cognitive and physical decline and behavior and mood changes. The most common forms of dementia are Alzheimer's disease and vascular dementia, followed by Lewy body dementia and frontotemporal dementia [1]. There is still no effective treatment that can influence the progression of Alzheimer’s disease and other dementia subtypes. Eventually, someone will die with or from dementia [2].

Most people with dementia live at home, often supported by spouses, adult children, or other family members [3]. Although the family often cares for them with love and dedication, family care can be a big burden [4,5]. For family caregivers it can, for instance, be stressful to deal with their relative’s behavior changes, such as dependent behavior, aggressive behavior, suspicious behavior, apathy or indifference, night-time restlessness, and masking behavior. These are often symptoms of the disease and are found in up to 90% of people with dementia [6,7]. Changes in behavior are “challenging” when this causes distress to the person with dementia and/or family caregivers and negatively affects the quality of life of at least one of these parties [8]. A Dutch study [9] found that about three quarters of the family caregivers of persons with dementia experienced problems in dealing with changes in the behavior or mood of their relative, in both the initial and later stages of the disease. In a recent focus group study, family caregivers reported that what they found most difficult was constantly having to switch between different strategies and that they had to keep their relative constantly occupied and distracted [10]. Furthermore, they found it stressful that other people often had a different view of the behavior and mood of the relative with dementia. Lastly, they also found it difficult that in theory they knew what to do in caring for their relative, but were often not able to put it into practice [10].

To support family caregivers (eg, in dealing with the relative’s behavior changes), an increasing number of self-management support interventions are being developed, some of which are Internet-based [11]. From the perspective of family caregivers, Internet support might be attractive, since they can use it at a time that is suitable for them, without travelling [12]. Boots et al [13] performed a systematic literature study of Internet-based support, such as a website with information and support on various aspects of care giving. The review by Boots et al [13] suggested that Internet-based support had positive effects (eg, regarding self-efficacy or other psychological and psychosocial outcomes for family caregivers). However, the review authors also concluded that the evidence was still scarce because of the low quality of the studies they had identified [13].

Previous research also did not provide a definitive answer about the effectiveness of incorporating personal contacts with a healthcare professional in online interventions, although some relevant studies have been conducted in this area [12,14-16]. For instance, in a study by Boots et al [14], face-to-face sessions with an experienced professional (psychologist or psychiatric nurse) and family caregivers were added to an online support intervention. The face-to-face sessions were seen as a valuable addition, as they provided an opportunity to tailor the support to the needs of the family caregivers and deepened the relationship [14]. In addition, Schaller et al [15] evaluated an interactive Web portal providing individualized information and support by dementia experts to family caregivers via a messaging function [17]. The interaction between family caregivers and experts was found to be useful, particularly because of the timely reaction to symptoms and because of the opportunity to reach immobile caregivers [15]. Comparable results were found in the study by Torkamani et al [16], which evaluated a computerized platform for contacts between the caregivers and health professionals aimed at reducing the burden on the caregiver, improving quality of life, and delaying institutionalization of the person with dementia. Furthermore, Blom et al [12] evaluated Internet-based information combined with online personal support. In this study, a psychologist provided online feedback on assignments about dealing with depression or other psychological problems in relatives of persons with dementia. The study by Blom et al [12] recommended further research to clarify the necessity of personal contacts with a professional; a completely self-help Internet program would be less expensive, which is an advantage in the current era with increasing numbers of persons with dementia and limited healthcare budgets. However, personal contacts with a healthcare professional might help people translate generic information to their own situation [12].

### Objectives

The aim of this study is to investigate whether a major intervention, consisting of personal email contacts with a specialized nurse in combination with videos and electronic bulletins (e-bulletins), is more effective than more minor interventions. Based on the results of this study we will be able to inform about which elements of online self-management support are effective (on their own or in combination) for family caregivers when managing changes in the behavior of their relative with dementia.

The research questions are (1) Is a major online self-management support intervention consisting of personal email contacts with a specialized dementia care nurse, videos, and e-bulletins more effective than smaller online interventions without personal email contacts, with regard to self-efficacy of family caregivers in managing the behavior changes of their relative with dementia, behavior problems in the persons with dementia, as reported by family caregivers, and positive and negative aspects of the relationship between the family caregiver and the person with dementia? (2) What background and baseline characteristics of family caregivers or the persons with dementia (eg, type of family relationship, baseline level of care pressure, and the specific behavior problems of the person with dementia) are associated with effects on the outcome variables mentioned in question 1? (3) How do the family caregivers evaluate the online self-management support intervention, with or without personal email contacts with a specialized nurse, regarding feasibility, usability, and satisfaction with the intervention?

## Methods

### Design and Randomization

To answer research questions 1 and 2, a randomized controlled trial (RCT) with 3 repeated measurements will be performed, involving the following intervention arms: (1) a major-intervention arm, (2) a medium-intervention arm, and (3) a minor-intervention arm.

Family caregivers will be randomly allocated to 1 of the 3 self-management intervention arms. Block randomization will be used to achieve balance in the allocation of participants to intervention arms [18]. An independent epidemiologist ([name]) prepared a randomization schedule to assign participants to an intervention arm, using several block sizes of 6 and 9. Following this randomization schedule, the researcher ([name]) will allocate participants to an intervention arm. The participants will then receive an email from the researcher ([name]) containing elements of the intervention arm in question. Participant and researcher blinding is not possible due to the nature of the intervention arms and the organization of the study.

Alongside the RCT, a process evaluation will be conducted to answer research question 3. For the process evaluation, a mix of qualitative and quantitative methods will be used.

### Power Calculation and Sample

We hypothesize that (1) both the major and medium intervention arms improve the self-efficacy as compared to the minor intervention arm; and (2) the major intervention arm gives better results for self-efficacy compared to the medium intervention arm. Considering a difference of 0.8 standard deviation units between the groups and assuming a significance level of .05, a power of 80%, and a correlation of .6 between the 2 repeated measures, 20 participants are needed per group. Taking into account a drop out percentage of 20%, we will include 24 participants per group.

In this study, providing self-management support through email is a relatively new task for the specialized nurses involved, with possible learning effects during the study. To take this into account, 1 extra block of 9 participants will be added to allow for a brief learning curve. Hence, in total 81 family caregivers of persons with dementia will be included.

The participants will be family caregivers of people with dementia who meet the following inclusion criteria: (1) the family caregiver is a relative of a person diagnosed with dementia (all types of dementia are eligible, with no restriction on the severity of the dementia); (2) the family caregiver must have contact with the person with dementia at least once a week; (3) the family caregiver's relative with dementia has to live at home (not in a care institution); (4) the family caregiver has access to the Internet and has basic skills in using the Internet and email; (5) the family caregiver has to be aged at least 18 years of age; and (6) the family caregiver is able to read and write Dutch.

To recruit family caregivers for our study, we will use several channels. The panel of the Dutch Alzheimer Society (in which more than 3000 informal caregivers participate) will be sent an email with an open call. Open calls will also be posted on the online forum of the Dutch Alzheimer Society (with 7000 monthly visitors), on the Dementie Nederlands website, and on the social media accounts (Facebook/Twitter) of the Dutch Alzheimer Society.

Recruitment via the aforementioned channels of family caregivers will proceed with first, a very short study description in the open call. In this description, family caregivers will be asked if they are interested in participating in the study. If so, they can send their name and email address to the principal researcher ([name]). The principal researcher will then send an email containing an information letter about the aims and procedures of the study to the family caregiver. This email will have a link to an online informed consent form, which the family caregiver can use to give their consent for participation. The participation flow chart is shown in Figure 1.

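### The 20% dropout allowance is taken as 20 × 1.2 = 24 instead of 20 / 0.8 = 25, so about 19.2 completers per group are expected, just below the 20 stated as needed

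*Protocol article*

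**What the plan says.** All the figures are in the protocol article, Power Calculation and Sample. The design inputs are "Considering a difference of 0.8 standard deviation units between the groups", "assuming a significance level of .05", 80% power and "a correlation of .6 between the 2 repeated measures". From these the article concludes that "20 participants are needed per group". The next sentence applies the allowance for loss: "Taking into account a drop out percentage of 20%, we will include 24 participants per group". One further block of 9 is added for the nurses' learning curve, and the paragraph ends: "Hence, in total 81 family caregivers of persons with dementia will be included". This total is 3 × 24 + 9, and the Abstract repeats it.

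Two rules under Analyses of Effects decide who counts towards the 20. The primary analysis takes randomised caregivers who completed follow-up, under the label modified intention-to-treat. The 9 caregivers in the learning-curve block are left out of it.

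**The concern.** Three figures stand side by side: 20 needed, 20% lost, 24 enrolled. They cannot all hold. A dropout percentage applies to the people enrolled, so the number remaining is the enrolled number times 0.80. To finish with 20, one divides by 0.80. Multiplying by 1.20 takes the 20% of the wrong base and always gives too few.

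The stake is the stated margin for attrition. A reader who takes the paragraph at face value believes that one participant in five can be lost with the required number still in hand. The true margin is one in six. With arms this small, that margin matters to anyone judging a null result, even though the shortfall is less than one person per group.

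**Working it through.** **Inputs (Power Calculation and Sample, unless noted)**
- Standardised difference 0.8; alpha .05 (sidedness not stated); power 80%; correlation .6 between 2 measures.
- 20 needed per group; 20% dropout; 24 enrolled per group; extra block of 9; total 81.
- Three arms (Design and Randomization).
- Completers analysed and block of 9 excluded (Analyses of Effects).

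**Step 1. Reproduce the 20.** Assume a two-sided test and the normal approximation, n = 2f[(1.960 + 0.842)/0.8]². The article gives no formula for the variance factor f.
- f = 1 (correlation ignored): n = 24.53.
- f = (1 + 0.6)/2 = 0.8 (mean of two measures) or f = 2(1 − 0.6) = 0.8 (change score): n = 24.53 × 0.8 = 19.62, rounded up to 20. This matches the article.
- f = 1 − 0.6² = 0.64 (one follow-up adjusted for baseline): n = 15.70, rounded up to 16.

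So f = 0.8 with a two-sided test is the natural reading, though it is inferred. A one-sided test with f = 1 also gives 20, but it makes no use of the stated correlation.

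**Step 2. Reproduce the 24.**
- 20 × (1 + 0.20) = 24, which matches the article.
- 20 / (1 − 0.20) = 25, which does not.

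Rounding does not rescue the figure: 19.62 / 0.80 = 24.53, which also rounds up to 25.

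**Step 3. What 24 delivers.**
- Expected completers at 20% dropout: 24 × 0.80 = 19.2 per group. This is below 20 and also below the unrounded 19.62.
- Dropout at which 20 remain: 1 − 20/24 = 4/24 = 16.7%.
- Matching size: 25 × 0.80 = 20.0.

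Steps 2 and 3 start from the article's own 20. Apart from the check against 19.62, they do not depend on sidedness or f.

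**Step 4. Effect on the totals.**

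| | As stated | Matching 20% dropout |
|---|---|---|
| Per group | 24 | 25 |
| Primary-analysis cohort (× 3) | 72 | 75 |
| Total with the block of 9 | 81 | 84 |

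**Step 5. Effect on power,** assuming a two-sided alpha of .05 and f = 0.8. By the normal approximation, power = Φ[(0.8/√0.8) × √(n/2) − 1.960].
- n = 20: Φ(2.828 − 1.960) = Φ(0.868) = 80.74%.
- n = 19.2: Φ(2.771 − 1.960) = Φ(0.811) = 79.14%.

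| Completers per group | Normal | t-based |
|---|---|---|
| 20 | 80.74% | 78.71% |
| 19.2 | 79.14% | 76.96% |
| Loss (points) | 1.60 | 1.75 |

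**Step 6. Sensitivity to f.** With f = 0.64, power at 19.2 per group is 87.3% (normal) or 85.5% (t-based). The dropout arithmetic is unchanged, but whether power falls below 80% depends on f.

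**The case against.** The strongest reply is that the error is real but hardly matters. The shortfall is 0.8 of a participant against the stated 20, and 19.62 − 19.2 = 0.42 against the unrounded requirement. The choice between the normal and t calculations moves power by about 2 points at n = 20 (80.7% against 78.7%), which is more than the dropout step does. This stands, and it is why the point is graded minor.

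A second reply concerns power. The article states neither a variance formula nor the sidedness, and Analyses of Effects plans mixed models adjusted for baseline differences. Under a baseline-adjusted factor of 0.64 the trial keeps about 87% power with 19.2 per group. This also stands. A reader might infer that the trial is underpowered, or that 79% is the power on the plan's own inputs. The documents do not support either, because 79% rests on an inferred factor. Only the 16.7% tolerance follows from stated numbers alone.

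A third reply is that those who drop out may not be wholly lost. The article does not say whether completing follow-up means the 6-week or the 12-week assessment, and it promises sensitivity analyses for missing data. That leaves some room, but the stated primary rule is completion, and a sensitivity analysis does not restore numbers to the primary one. The block of 9 offers no reserve either, since it is excluded.

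Finally, the sample size could no longer change: the article's Results section reports data collection complete in August 2017, and publication followed in November 2017. This is correct and bears on the remedy. It does not make the printed sentence consistent.

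**Conclusion.** The point holds as an arithmetic error with a small effect. Given the article's own 20 per group and 20% dropout, 24 is one too few per group: 25 matches, with 75 instead of 72 in the primary analysis and 84 instead of 81 in total. At 20% dropout the expected number of completers is 19.2 per group, and 24 enrolled tolerates 16.7% loss. These figures need no assumption beyond reading dropout as a share of those enrolled and applying the stated completer rule.

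The power loss is about 1.6 to 1.8 points, to roughly 79% (normal approximation) or 77% (t-based), conditional on a two-sided test and f = 0.8.

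Two stronger readings should be set aside. A reader might infer that the enrolled size itself is below 20; it is 24, and only the expected completers fall short. A reader might also infer that every figure in the chain is wrong. The 20 is reproduced and is not in question on this point; only the 24, and the 81 built on it, fail to match a 20% allowance. No hypothesis, outcome or analysis set is affected.

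**What to change.** Reword the dropout sentence under Power Calculation and Sample. It should say that 24 per group (72 in the primary analysis, 81 in total with the learning-curve block) yields 20 completers per group only if dropout is at most 16.7% (4 of 24), and that about 19 per group are expected at 20% dropout. It may add that 25 per group, 84 in total, would have been the size matching 20%.

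Any power figure given for 19 completers should carry its assumptions: two-sided .05, variance factor 0.8, and whether it is normal or t-based.

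The cost is one sentence and a slightly less favourable attrition margin. No extra enrolment is asked for, and the 24 and 81 can stand as the numbers planned.

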### Intervention Arms and Components

In the RCT, 3 intervention arms will be studied, all focusing on self-management support in dealing with behavior changes, but varying in the number of elements. The intervention arms are referred to as major, medium, and minor.

#### Major Self-Management Support Intervention

The major intervention arm consists of the following elements: (1) 3 personal email contacts with a nurse specialized in dementia care, (2) provision of online videos about how to manage behavior changes in a relative with dementia and to improve your self-efficacy in managing with this behavior, and (3) provision of e-bulletins with practical information about different types of behavior changes and how to manage them.

The personal email contacts will be handled by a nurse with a Bachelor’s or Master’s qualification in nursing and with follow-up training in dementia care. In the email contact, the nurse will support the family caregiver in managing behavior changes. The nurse will also give feedback on assignments and will give feedback on the plan that the family caregiver came up with in the assignments. The nurse will tailor their support to the personal needs and questions of the family caregiver, while guided by an intervention protocol developed by project group members ([name], [name], [name], [name]), in consultation with the nurses who had to use the intervention protocol. The number of email contacts was discussed and agreed with experts in dementia care who have experience with online support. Three email contacts are thought to be sufficient and feasible.

**Figure 1 figure1:**
[figure not shown]
Study flow chart.

The Dutch-language intervention protocol (available on request from the first author) is based on the 5 steps of the “5A model” of self-management support [19] and the person-centered care theory of Kitwood [20]. The “5A model” consists of the following steps: (1) assessing the state of behavior, beliefs, and motivation; (2) advising based upon personal health risks; (3) agreeing on a realistic set of goals; (4) assisting in anticipating barriers and developing a specific action plan; and (5) arranging follow-up [19,21,22].

There are 6 videos about different types of behavior changes that occur frequently (dependent behavior, aggressive behavior, suspicious behavior, apathy or indifference, nighttime restlessness, and masking behavior). Family caregivers can choose the number of videos they watch and the accompanying assignments that they do themselves, depending on their own needs and the behavior changes that occur in their relative with dementia. The videos (as well as the e-bulletins mentioned below) were developed by the Trimbos Institute, of which 2 of the developers are involved in the present study ([name], [name]), in close cooperation with the Dutch Alzheimer’s society, other dementia experts, and family caregivers of people with dementia. As a first step in the development trajectory, a desk search was performed to gain insight into what is known in the literature about how family caregivers perceive different types of behavior changes in their relative with dementia and the theory of person-centered care [20]. Experts also provided input for the components of the videos (eg, principles of cognitive behavioral therapy [CBT], modeling, persuasive communication, and active learning). At several stages in the development trajectory, video scripts and pilot videos were tested by family caregivers.

The behavior changes covered in the bulletins are the same as in the videos. The e-bulletins involve assignments to help caregivers translate the generic information to their own situation and to reflect on possible causes of the behavior changes, how they want to influence the behavior, and how they want to cope with it. The e-bulletins were tested in conjunction with the testing of the videos and they also have the same theoretical base as the videos.

